# The effect of perioperative intravenously administered iron isomaltoside 1000 (Monofer®) on transfusion requirements for patients undergoing complex valvular heart surgery: study protocol for a randomized controlled trial

**DOI:** 10.1186/s13063-018-2545-3

**Published:** 2018-07-04

**Keywords:** Complex valvular heart surgery, Iron isomaltoside 1000, Anemia, Transfusion

## Abstract

**Background:**

Anemia is a frequent complication after cardiac surgery especially following reoperation due to previous prosthetic valve failure or multiple valve surgery (including combined coronary artery bypass grafting). This trial explores whether intravenously administered iron isomaltoside 1000 (Monofer®) results in better clinical outcomes in patients undergoing complex heart valve surgery who are expected to receive transfusion.

**Methods/design:**

In this prospective, single-center, double-blinded, randomized controlled trial, 214 patients undergoing reoperation or multiple valve surgery are randomly allocated to either the iron isomaltoside 1000 (IVFe) or the control group from August 2016 to August 2018. The IVFe group receives iron isomaltoside 1000 mg (maximum dose 20 mg/kg) intravenously 3 days before and after the surgery. The control group receives an equivalent volume of normal saline. The primary endpoint is transfusion requirement (more than 1 unit of packed erythrocytes) for postoperative care until discharge and secondary endpoint are major complications, such as delayed ventilator therapy, acute kidney injury, and mortality. Reticulocyte count, plasma hepcidin, iron profiles (serum iron, serum ferritin, total iron-binding capacity, transferrin, transferrin saturation), coagulation profiles, urinary analysis, and chemical profiles are measured for three preoperative baseline-data days and just before surgery, except for hepcidin. After surgery, daily routine basic laboratory tests are measured just before discharge and reticulocyte count, iron profiles, and hepcidin are repeatedly checked for three postoperative days.

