### Study objective and outcomes (primary and secondary outcomes)

The primary objective of the trial is to demonstrate that IVFe is superior compared to placebo in leading to less decrease in the Hb level and reducing the need of transfusion in patients undergoing complex cardiac surgery, which is a highly possible scenario for receiving a transfusion. The secondary objectives are to compare the effects of IVFe on the clinical (or surgical) outcomes (e.g., renal failure, respiratory failure, etc.) from reducing the need for blood transfusion and the stability of iron-related parameters. The final objective is to assess the role of the iron-regulatory protein, hepcidin, as a biomarker, as well as any association of hematological parameters with outcome. Thus, we decided the endpoints as followings: the primary endpoint is the comparison of perioperative transfusion requirements in terms of overall incidence and mean amounts of units of packed erythrocytes transfused per patient during and after the operation until discharge, and the secondary endpoint is the occurrence of postoperative major advanced complications (delayed ventilator therapy, AKI and all-cause mortality). A Hb concentration of less than 7 mg/dl during CPB, and less than 8 mg/dl after CPB and postoperatively, were used as transfusion thresholds. Intraoperatively, we measured the Hb concentration post induction and every 30 min during CPB, then at 10 min post CPB and post sternal closure, and postoperatively at the time of, and 8 h after, arrival at the ICU. After the day of surgery, we measured the Hb concentration in the morning if there was no excessive bleeding (over 1000 cm^3^) or symptoms of anemia. Any patients who have Hb concentrations higher than 8 mg/dl postoperatively, yet required transfusion due to symptoms of acute anemia, such as shortness of breath, change in respiratory rate and pulse rate, mental function deterioration, and myocardial ischemia, were excluded from the study. We also excluded patients who had undergone re-exploration for postoperative bleeding (postoperative bleeding was defined by total drainage volume (< 1000 cm^3^) during the 4 h after arrival in ICU).

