Postoperative variables included the amount of bleeding measured by chest-tube drainage after surgery, fluid input, urine output, and overall amount of ABT. Hb concentrations, PT, AST/ALT, and creatinine (Cr) levels were measured preoperatively, post anesthetic induction, and postoperative day (POD) 0 (day of the surgery after arrival in the ICU), 1, 2, 3, 4, and 7. Reticulocyte count and iron profiles were measured preoperatively and post anesthetic induction and at POD 3, and POD 10, and the changes in reticulocyte count from the baseline values were calculated. Postoperative variables also included the incidence of perioperative transfusion volume, the incidence of AKI within 48 h after surgery, new-onset AF after surgery, duration of ventilator care, ICU stay and hospital stay, and in-hospital mortality. Multiple ABT is defined as more than 1 unit of packed erythrocytes during the operation and until discharge. AKI is defined as elevation of serum Cr of ≥ 0.3 mg/dl or 50–200% from baseline using the modified Risk, Injury, Failure, Loss, and ESRD classification [14]. Surgical mortality is defined as all deaths that occur during the hospital stay or after hospital discharge but within 30 days postoperatively.

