### Statistical methods

Continuous variables were shown as means ± standard deviation (SD) and dichotomous variables are shown as numbers (percentages). Between-group comparisons of continuous variables were performed using the independent Student *t* test. Dichotomous variables were compared using the chi-square or Fisher’s exact tests, as appropriate. *P* values < 0.05 will be considered statistically significant.

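### The primary endpoint is defined in two incompatible ways (unit cut-off, type of measure, time window), so the trial's main result is not uniquely defined

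*Protocol article*

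**What the plan says.** The protocol article describes the primary endpoint in two places.

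- **Abstract, Methods/design:** "The primary endpoint is transfusion requirement (more than 1 unit of packed erythrocytes) for postoperative care until discharge". This is one binary measure, with a cut-off above 1 unit and a postoperative window.
- **Study objective and outcomes:** "the primary endpoint is the comparison of perioperative transfusion requirements in terms of overall incidence and mean amounts of units of packed erythrocytes", with the window given as "transfused per patient during and after the operation until discharge". These are two measures, one a proportion and one a mean, and the window includes surgery.

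Three other statements bear on the question.

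- Later in the outcomes section, among the postoperative variables: "Multiple ABT is defined as more than 1 unit of packed erythrocytes during the operation and until discharge". Here the abstract's cut-off belongs to a separately named variable, with a window different from the abstract's.
- The primary objective is to show that "IVFe is superior compared to placebo in leading to less decrease in the Hb level and reducing the need of transfusion". The null hypothesis under Sample size likewise couples Hb level with transfusion need.
- Statistical methods assigns t tests to continuous variables and chi-square or Fisher tests to dichotomous ones, with one general threshold: "values < 0.05 will be considered statistically significant".

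**The concern.** A primary endpoint should let two people with the same dataset reach the same verdict. Here they could not. One following the abstract would compare the proportions given more than 1 unit after surgery. One following the main text would compare an incidence and a mean number of units, both counted from the operation onward. The cut-off, the type of measure and the window all differ, so this goes beyond an abstract dropping detail. Nor can more than 1 unit be loose wording for any transfusion, since the outcomes section treats it as a variable of its own.

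At stake is whether a reported success answers a question fixed in advance. If the definition can be settled after the data are seen, or if either main-text measure suffices, the nominal 5% error rate no longer holds.

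**Working it through.** **1. Do the definitions classify patients differently?** Read overall incidence as at least 1 unit. This is the natural reading, but the article does not state it.

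| Packed erythrocytes received | Abstract (>1 unit, postoperative) | Main text (incidence, surgery included) | Multiple ABT (>1 unit, surgery included) |
|---|---|---|---|
| 1 unit postoperatively | no | yes | no |
| 3 units in theatre only | no | yes | yes |
| 1 unit in theatre, 1 postoperatively | no | yes | yes |
| 2 units postoperatively | yes | yes | yes |

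The three classifications agree only in the last row. Mean units is not a classification at all and would be tested by a t test.

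**2. Does the sample size reveal which measure was meant?** Stated inputs (Sample size): two-sided 0.05, 80% power, effect size 0.5, normally distributed data, a 40% transfusion rate, an earlier 35% reduction, and 97 per group.

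- As a standardised mean difference: n = 2(1.96 + 0.84)² / 0.5² gives 63 per group.
- As two proportions, n = [1.96√(2p̄(1−p̄)) + 0.84√(p₁(1−p₁)+p₂(1−p₂))]² / (p₁−p₂)². For 40% vs 20% (0.5 read as halving) this gives 82. For 40% vs 26% (40% × 0.65) it gives 176.
- The formula returns exactly 97 for 60% vs 40%, a pair the article does not state.
- The dropout step does reproduce: 97 × 1.10 = 106.7, rounded to 107.

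So 97 does not follow from the stated inputs under either reading, and the calculation cannot show which measure is primary.

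**3. Error rate if any one measure suffices.** With independent tests at 0.05:

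- two measures: 1 − 0.95² = 9.75%
- three measures: 1 − 0.95³ = 14.3%

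The measures are correlated, so the true figures are lower. They were simulated with no treatment effect and 97 per group. Units were gamma-Poisson with mean 0.6 in theatre and 0.8 postoperatively, sharing a patient-level gamma factor of shape 0.5, 1 or 3. There were 4,000 trials in each of six runs. All of these settings are assumptions.

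- Each test alone: 4.4 to 5.5%.
- Incidence or mean units: 8.3 to 9.3%.
- Adding >1 unit postoperatively: 11.1 to 11.9%.

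In that model the any-transfusion rate, 1 − (1 + 1.4/k)^(−k) for shape k, is 49%, 58% and 68%, above the article's 40%. A different model set at 40% transfused (6,000 trials) gave 8.3% for the two main-text measures. A further null simulation gave about 8%, and about 10% with >1 unit added. Across models the ranges are therefore about 8 to 9% and about 10 to 12%.

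**4. Other success rules.** If every measure had to be significant, the error rate would not exceed 5%, and joint power could not exceed that of the weakest measure. If either sufficed at a Bonferroni level of 0.025, 40% vs 20% would need 99 per group, and 97 would give 79.3% power.

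**The case against.** The strongest defence is that this is a journal article. A success rule, a testing order or a split of alpha is commonly left to an analysis plan, which is not shown, and the 0.05 sentence is a general threshold rather than a decision rule. That stands: their absence is not the point here. It does not answer the conflict between the abstract and the outcomes section, because both statements are in this document and cannot both be the primary endpoint.

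Some stronger readings are tempting but not supported.

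- **Hb as a further primary endpoint.** A reader might infer this from the objective and the null hypothesis. But the outcomes section goes on from its objectives to name the endpoints, and the primary one concerns transfusion only. Error rates of 12.6% (Hb added to the two main-text measures) or about 15 to 16% (Hb and >1 unit both added) belong to families of tests that the article never sets out.
- **Type I error is definitely inflated.** It is inflated only under an either/or rule or a free choice of definition. The article states neither and excludes neither.
- **Including surgery ruins the power.** This depends on how many transfusions occur in theatre, which the article does not give. Suppose 40% are transfused, theatre transfusions are unaffected and the rest fall by 35%. Power at 97 per group then runs from 44% (5 of the 40 points in theatre) to 7% (30 of the 40). The assumption of no effect in theatre is itself doubtful, since the first infusion precedes surgery. A postoperative window would also include days before the second infusion, so timing does not clearly favour either window.

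**Conclusion.** The point holds as an internal contradiction, and that part needs no assumption: cut-off, measure and window differ between the abstract and the outcomes section, and nothing else in the article settles which applies. Hb adds a lesser misalignment, between the objective and null hypothesis on one side and the endpoint sentences on the other.

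The error-rate consequence is conditional. It is about 8 to 9% if either main-text measure may count, and about 10 to 12% if the abstract's version may also be chosen. Both ranges depend on assumed unit distributions. A reader should not conclude that the trial has a fixed inflated error rate, or that it has three or four co-primary endpoints. What can be concluded is that the primary verdict is not uniquely determined by the document.

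**What to change.** Before unblinding, name one primary endpoint with one cut-off and one window. One option that keeps closest to the outcomes section is the proportion of patients receiving at least 1 unit of packed erythrocytes from the start of surgery to discharge, tested at two-sided 0.05. Make mean units, >1 unit and Hb secondary. A fixed testing order for these, and a breakdown of transfusion by period, are optional.

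Align the abstract, primary objective, null hypothesis, outcomes section (including the multiple ABT definition) and Sample size section with that choice. Restate the sample-size basis for the chosen endpoint. For a proportion, the answer depends on the intended effect: 97 per group gives about 87% power for 40% vs 20% but about 55% for 40% vs 26%, and the article does not say which pair applies.

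The cost is amendment wording and the loss of the option to claim success on mean units or >1 unit alone. Study status reports recruitment as incomplete at submission, so the change was feasible then. If the data have since been unblinded, the choice is no longer neutral, and results under every stated definition should be reported side by side.

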**Discussions:**

From our study, we can clarify the following points: the first is the perioperative IVFe effect on the demand for transfusion, and clinical outcomes in reoperation or complex valve surgery and the second is the role of hepcidin in the effect of IVFe on the hemoglobin level increase.

**Trial registration:**

ClinicalTrials.gov, Identifier: NCT02862665. Registered on August 2016.

**Electronic supplementary material:**

The online version of this article (10.1186/s13063-018-2545-3) contains supplementary material, which is available to authorized users.

## Background

Anemia is a common postoperative disorder in cardiac surgery patients after cardiopulmonary bypass (CPB) [1, 2]. Allogeneic blood transfusions (ABT) with red blood cells, which should be avoided whenever possible, is associated with complications [3] because ABT carries increased risks for transmission of infectious diseases and has been clearly demonstrated to be associated with adverse outcomes related to postoperative acute kidney injury (AKI), neurological complications, atrial fibrillation (AF), acute lung injury, and increased mortality [4–6]. So, many strategies have been developed to minimize the need for ABT, but transfusion requirements still remain high [3].

In patients with cardiovascular disease, iron deficiency is common either due to depletion of whole-body iron stores (absolute iron deficiency) or because of restricted availability of iron for erythrogenesis (functional iron deficiency). Thus, iron therapy is commonly used to reinforce the iron reserve to prevent anemia after bleeding; however, the effect of iron replacement after cardiovascular surgery is not clear. Iron plays an essential role in erythropoiesis and hemoglobin (Hb) synthesis [7]. The route of iron administration and the type of iron preparation vary widely. The effectiveness of iron supplement administration per os is often limited by its gastrointestinal side effects (10–40%) and low absorption rate (10–15%) [8, 9]. Therefore, some authors have suggested a role for intravenously administered (IV) iron in correcting anemia after orthopedic and oncological surgery, and in renal and obstetric patients [10, 11], but this route still remains controversial in cardiac surgery. In addition, the iron-regulatory protein, hepcidin, is responsible for controlling dietary iron absorption and body iron distribution [12]. Hepcidin acts by binding to the iron transport protein ferroportin, blocking iron absorption from the intestine and iron release from macrophages, leading to reduced iron delivery to erythroid precursors [13]. This hepcidin’s role under IV iron replacement also remains unclear in patients undergoing cardiovascular surgery.

Therefore, in this study, we tried to investigate the effect of the perioperative administration of IV iron isomaltoside 1000 (Monofer®; Pharmacosmos, Holbaek, Denmark) in patients undergoing re-do or a complicated valve replacement such as coronary bypass grafting (CABG) combined, or cases of multiple valve replacement and arrhythmia surgery combined. We also tried to assess the role of hepcidin as a biomarker, as well as any association of hematological parameters with outcome.

## Methods/design

### Study design

This prospective, double-blind, placebo-controlled, randomized, comparative, single-center trial was planned in Severance Cardiovascular Hospital, Seoul, Korea from August 2016 to August 2018 in patients undergoing re-do (re-do, second re-do, etc.) – or complicated valve replacement (double valve – aortic, mitral, with or without tricuspid surgery, CABG combined, arrhythmia surgery combined) cases. The trial protocol and related documents were approved by the competent authorities and Institutional Review Board (IRB) of the University of Yonsei (approval number: 4-2016-0502). The trial was conducted in accordance with Good Clinical Practice and the Declaration of Helsinki. Informed consent was obtained in writing prior to any trial-related activities. This trial was registered at ClinicalTrials (ClinicalTrials.gov, Identifier: NCT02862665) in August, 2016.

Patients will be randomly allocated to either the IV iron isomaltoside 1000 (IVFe) or the control (normal saline) group in a 1:1 ratio by means of computer-generated random numbers. IVFe administration is scheduled at 3 days before and after surgery. The patients will be checked by laboratory testing five times perioperatively at: (1) the preoperative baseline visit: reticulocyte count, Hb, plasma hepcidin, iron profiles (serum iron, serum ferritin, total iron-binding capacity, transferrin, transferrin saturation), coagulation profiles (PT, PTT), routine urinary analysis, and chemical profiles (aspartate aminotransferase (AST)/alanine aminotransaminase (ALT), serum creatinine, electrolytes, C-reactive protein (CRP), creatine kinase (CK), estimated glomerular filtration rate (GFR)), (2) start of therapy (first injection of IVFe 3 days before surgery): repeat laboratory test except for plasma hepcidin, (3) postoperative day 3 (just before the second injection of IVFe): repeat laboratory test except for urinary analysis, (4) postoperative day 10 or discharge day: repeat laboratory test except for plasma hepcidin and urinary analysis, and (5) postoperative week 4: repeat laboratory test except for plasma hepcidin and urinary analysis (Table 1).

**Table 1 Tab1:** Perioperative laboratory data sheet

	Lowest Hb/HCt	reticulocyte count	Highest PT (sec/INR)	Highest PTT	Highest GOT/GPT	Highest Cr	U/A RBC(±)	Serum iron	Transferrin sat (%)	Ferritin (ng/ml)	TIBC^a^	Hepcidin
Before surgery 2–3 days	/		/		/		(±)					
Just before surgery	/		/		/		(±)					
POD0	/		/		/		(±)					
POD1	/		/		/		(±)					
POD2	/		/		/							
POD3	/		/		/							
POD4	/		/		/							
POD5	/		/		/							
POD6	/		/		/							
POD7	/		/		/							
POD10 or discharge day	/		/		/							
Follow-up OPD (20)	/		/		/							

*U/A RBC* Urinary analysis red blood cells, *GOT* Glutamic Oxalacetate Transaminase, *GPT* Glutamic Pyruvate Transaminase

*Cr* creatinine, *Hb* hemoglobin, *HCt* hematocrit, *INR* International Normalized Ratio*, OPD* outpatient department, *OT, POD* postoperative day*, PT* prothrombin time, *PTT* partial thromboplastin time, *TIBC* total iron-binding capacity*, U/A RBC* Urinary analysis red blood cells.

The IVFe group received iron isomaltoside 1000 as a single-dose infusion of 1000 mg over 30 min with a maximum single dose of 20 mg/kg. The placebo group received saline (0.9% Sodium Chloride Injection; JW Pharmaceutical, Seoul, Korea) as a single-dose infusion of 100 ml over 30 min.

### Participants and eligibility criteria

Basically, all patients aged 19 years of age or older undergoing re-do (re-do, second re-do, etc.) – or a complicated valve replacement (double valve – aortic, mitral, with or without tricuspid surgery, CABG combined, arrhythmia surgery combined cases) are included. Eligibility will be determined by two cardiac surgeons and two cardiac anesthesiologists on the basis of the preoperative evaluation results. After completing the screening, participants will be guided through the informed consent process and written informed consent will be obtained from all participants before the initiation of any preoperative iron treatment. After consent forms are signed, participants will be randomly allocated to one of the two groups in a 1:1 ratio (Fig. 1).

**Fig. 1 Fig1:**
[figure not shown]
Schematic of study design

### Exclusion criteria

Exclusion criteria are as followings: (1) patients who have critical anemia that cannot be corrected by only iron replacement therapy (Hb < 9 g/dl for women and Hb < 10 g/dl for men) such as aplastic anemia, (2) patients who have end-stage renal disease (ESRD) treated with erythropoietin or any concomitant medication for erythropoiesis, (3) patients with previous paravalvular leakage, because any ensuing hemolytic anemia cannot be corrected by iron replacement, (4) patients with a hyperallergic reaction to iron agents, and aplastic anemia, and (5) patients who have been treated in intensive care unit for severe cardiac dysfunction.

### Randomization

Patients are randomly allocated to either the IV iron isomaltoside 1000 (IVFe) or the control (normal saline) group in a 1:1 ratio by means of computer-generated random numbers. Random numbers will be generated by an independent statistics professional using SPSS version 19.0 for Windows (release 19.0 K; SPSS Inc. Armonk, NY, USA). Sealed assignment envelopes will be used for allocation concealment.

### Withdrawal and dropout

All participants will have the right to withdraw from the study at any time. Participation will be terminated if the individual wants to stop and withdraws consent. The trial will be stopped if the investigator believes that there are unacceptable risks to participants. If any patients show typical complications of IVFe, such as nausea, vomiting, hypotension, gastric discomfort, urticaria, and acute renal failure, participation will be terminated immediately. The patients who have Hb concentrations higher than 8 mg/dl postoperatively, yet require transfusion due to symptoms of acute anemia, such as shortness of breath, change in respiratory rate and pulse rate, mental function deterioration, and myocardial ischemia, are excluded from the study. Patients with postoperative paravalvular leakage should be removed to avoid confusion with the possibly similar effects on red blood cells as hemolytic anemia. Postoperative gastrointestinal bleeding is excluded. We also excluded patients who underwent re-exploration for postoperative bleeding (postoperative bleeding is defined as total drainage volume < 1000 cm^3^ during the 4 h after arrival in the intensive care unit (ICU)).

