### Data collection

We will collect the clinical data from the laboratory results of all enrolled patients during admission and at outpatient clinic follow-up.

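### A listed complication of iron ends trial participation, not only study dosing, and nothing commits the trial to collecting transfusion, ventilation and mortality data afterwards

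*Protocol article*

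**What the plan says.** The rule is in the protocol article under Withdrawal and dropout: "If any patients show typical complications of IVFe, such as nausea, vomiting, hypotension, gastric discomfort, urticaria, and acute renal failure, participation will be terminated immediately". Shortly before it, the same section says of patients who change their mind: "Participation will be terminated if the individual wants to stop and withdraws consent". The section does not separate stopping the study drug from leaving the study.

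The outcomes run well beyond the likely time of such an event. Under Study objective and outcomes:

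- The primary endpoint covers the incidence of transfusion and the "mean amounts of units of packed erythrocytes transfused per patient during and after the operation until discharge".
- For complications, "the secondary endpoint is the occurrence of postoperative major advanced complications (delayed ventilator therapy, AKI and all-cause mortality").
- The postoperative variables include "the incidence of AKI within 48 h after surgery".
- For deaths: "Surgical mortality is defined as all deaths that occur during the hospital stay or after hospital discharge but within 30 days postoperatively".

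The two infusions are scheduled three days before and three days after surgery (Intervention).

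The only general statement on follow-up is under Data collection: "We will collect the clinical data from the laboratory results of all enrolled patients during admission and at outpatient clinic follow-up".

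**The concern.** Stopping an infusion after a reaction protects the patient. Ending participation adds no protection and may end observation of the outcomes the trial was set up to compare.

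The trigger occurs after randomization and may depend on treatment. Some of the listed events, such as hypotension and acute renal failure, are also signs of a difficult postoperative course, in which more transfusion is plausible. If follow-up stops there, data are lost in patients whose outcomes probably differ from the rest, possibly at different rates in the two arms. The patients left would then no longer be the groups formed by randomization. An analysis plan can define populations and imputation, but it cannot bring back data that were not collected.

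Timing adds to this. A reaction to the first infusion could end participation before the operation, so that none of the primary outcome is observed. Acute renal failure in the first two days after surgery could end it before the second infusion, while transfusion, ventilation and mortality are still accruing.

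**Working it through.** **Reading the text.** Three statements bear on the question.

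1. Withdrawal and dropout uses the same wording for a listed complication as for withdrawn consent. In the second case it must mean leaving the trial, so that is the plain meaning in the first.
2. Data collection speaks of all enrolled patients during admission and at outpatient follow-up, but names laboratory results only. Transfused units, ventilator time and deaths are not laboratory results, and terminated patients are not mentioned.
3. Study objective and outcomes counts transfusion to discharge and deaths to 30 days. It does not say that either continues to be recorded after termination.

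The documents therefore state the exit and give no commitment that offsets it.

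**Allowance for losses.** Sample size gives 97 per arm, raised to 107 for dropout (97 × 1.1 = 106.7). The allowance is 107 − 97 = 10 per arm, or 10/107 = 9.3%, for all causes, including the other removals in Withdrawal and dropout. The point does not depend on how 97 was obtained.

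**Illustration of bias.** The document gives no complication rates, so the rates below are assumptions. Let p be the transfusion risk in the whole arm, t the share terminated and q the transfusion risk among those terminated. If terminated patients are left out, the risk among those who remain is

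(p − t·q) / (1 − t).

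Take p = 0.40 in both arms, so that there is no true effect. The 40% is borrowed from Sample size.

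| q | t = 10% | t = 5% | Difference |
|---|---|---|---|
| 0.70 | (0.40 − 0.070)/0.90 = 36.67% | (0.40 − 0.035)/0.95 = 38.42% | −1.75 points |
| 0.90 | (0.40 − 0.090)/0.90 = 34.44% | (0.40 − 0.045)/0.95 = 37.37% | −2.92 points |

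- With 10% terminated on iron and 5% on saline, iron looks better by 1.8 to 2.9 points.
- With the rates reversed, iron looks worse by the same amount.
- With equal t and q in the two arms, the difference is 0.
- If terminated patients have the average risk (q = 0.40), the formula returns 0.40 for any t, so there is no bias. The bias needs both unequal termination and a different risk in those terminated.

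**Against sampling error.** With 107 per arm before termination, 96.3 and 101.65 remain. For q = 0.70 the standard error is √(0.3667 × 0.6333/96.3 + 0.3842 × 0.6158/101.65) = 6.9 points; for q = 0.90 it is 6.8. The shifts are about 0.25 and 0.43 standard errors, and the two-sided type I error rises from 5% to about 5.7% and 7.1%.

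**Dilution under the remedy.** If a share d of the iron arm misses the second dose and loses a share s of its benefit, the treatment contrast shrinks by d·s. With d = 5% to 10%, this is 2.5% to 5% of the contrast for s = 0.5, and 5% to 10% for s = 1.

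**The case against.** The strongest reply is that the harmful step is inferred. The same section says that other groups are excluded from the study or should be removed, whereas for complications it says only that participation ends. It does not say that their data are discarded or that they leave the comparison. Data collection refers to all enrolled patients with no exception, and admission covers the whole primary endpoint window. Analysis populations are commonly fixed in a full protocol or analysis plan that is not shown.

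Much of this stands. A reader might infer that the trial drops these patients from the analysis; the article does not say so. What remains is narrower: the article ends participation and commits to nothing but laboratory results afterwards.

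A reader might also infer that the AKI endpoint is lost because acute renal failure is a trigger. That does not follow. A renal failure that triggers termination has normally already met the AKI definition and can be counted. Later transfusion, ventilation and death are what is at risk.

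A third objection is that the rule concerns typical complications of iron, which implies attribution to the drug, so few patients may be affected. That is possible, and the number is unknown. It does not remove the concern: exits limited to true drug reactions would fall mainly in the iron arm, while a looser reading would take patients with non-specific postoperative signs from both arms. Finally, the trial is described as double-blind, and the illustrated shifts are small beside the standard error. Both are fair reasons to keep the point in proportion.

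**Conclusion.** The point holds as a risk created by the stated conduct rule. It is not a demonstrated bias. The text ends participation after a listed complication, and nothing in the article secures transfusion to discharge, ventilation or 30-day mortality from then on.

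Size and direction cannot be determined from the documents. The 1.8 to 2.9 points rest on assumed termination rates of 10% and 5%, an assumed 70% to 90% transfusion risk in those terminated, and their omission from the comparison. The documents do not support a claim that the result would be tilted towards iron: reversing the rates reverses the sign, and equal rates give zero. The sponsor should make the change because it is cheap and leaves patient safety as it is. Confidence is moderate, because the wording is clear but the consequence depends on rates and handling that are not reported.

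**What to change.** Reword the sentence under Withdrawal and dropout so that any listed complication, including acute renal failure, stops further study infusions only. The stop on dosing stays exactly as now. The patient remains in follow-up for transfusion to discharge, AKI, ventilation and mortality to 30 days, and is analysed in the randomized arm, unless consent is withdrawn. A renal failure that meets the article's AKI definition is counted as AKI.

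For patients already terminated under the rule who did not withdraw consent, retrieve these outcomes from hospital records, with ethics approval. The article appeared in July 2018, recruitment was incomplete at submission, and the trial was planned to run to August 2018. Unless it overran, retrieval may be the main practical gain.

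The cost is a late amendment, the record retrieval, and a slight dilution from patients who receive only one of the two doses. No patient is dosed under a different rule.
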